## G.7 Provisions to Monitor the Study to Ensure the Safety of Subjects

1. *Describe the plan to periodically evaluate the data regarding both harms and benefits to assess subject safety as follows:*
   1. *The data that will be reviewed, including safety data, untoward events, and efficacy data:* NA. There is no planned safety data as the intervention is a non-invasive study that will not affect the participants clinical care. No interim analysis is planned for assessment of efficacy.
   2. *Who will review the data:* NA
   3. *How the safety information will be obtained and documented (e.g., case report forms, by telephone calls with participants, printouts of laboratory results, etc.):* NA
   4. *The frequency of data collection, including when safety data collection starts:* NA
   5. *The frequency or periodicity of review of cumulative data:* NA
   6. *The statistical tests for analyzing the safety data to determine whether harm is occurring:* NA
   7. *Any conditions that trigger an immediate suspension of the research or other action for the research:* NA

The plan might include establishing a data monitoring committee which addresses all the above.

1. *Describe the entity responsible for monitoring the data, and their respective roles (e.g., the investigators, the research sponsor, a coordinating or statistical center, an independent medical monitor, a Data and Safety Monitoring Board (DSMB) /Data Monitoring Committee (DMC), and/or some other entity, and the timeframe for reporting events to this entity:* NA
2. *A copy of the DSMB/DMC Charter if the study is enclosed with the submission:* Yes N/A

## G.8 Vulnerable Populations

If the research involves individuals who are vulnerable to coercion or undue influence, describe the rationale for their inclusion and the additional safeguards included to protect their rights and welfare.

- 1. Can or will pregnant women be enrolled?

**Yes  No**

- 1. Can or will the research involve neonates of uncertain viability or non-viable neonates?

**Yes  No**

If **Yes**, respond to all of the following:

1. Any preclinical and clinical studies that have been conducted that provide data for assessing potential risks to neonates:
2. The important biomedical knowledge that will be developed from this research and why it cannot be obtained by other means:
3. Whether there will be added risk to the neonate resulting from the research:
4. How individuals providing consent are informed of the reasonably foreseeable impact of the research on the neonate:
5. No person shall perform or offer to perform an abortion where part or all of the consideration for said performance is that the fetal remains may be used for experimentation or other kind of research or study: Yes  N/A
6. No person shall knowingly sell, transfer, distribute or give away any fetus or neonate for a use which is in violation of [Massachusetts General Laws Chapter 112 Section 12J](https://malegislature.gov/Laws/GeneralLaws/PartI/TitleXVI/Chapter112/Section12J): Yes  N/A
7. Individuals engaged in the research will have no part in determining the viability of a neonate:

Yes  N/A

1. For non-viable neonates, the vital functions of the neonate will not be artificially maintained and that the research will not terminate the heartbeat or respiration of the neonate: Yes  N/A
2. For neonates of uncertain viability, the research holds out the prospect of enhancing the probability of survival of the neonate to the point of viability, and any risk is the least possible for achieving that objective: Yes  N/A
3. Can or will subjects who are not yet adults (neonates, children, teenagers) be enrolled?

**Yes  No**

If **Yes**, respond to all of the following:

1. Check to confirm that you will follow “[SOP: Legally Authorized Representatives, Children, and Guardians (HRP-013)](http://viceprovost.tufts.edu/HSCIRB/files/HRP-013_SOP_Legally-Authorized-Representatives-Children-Guardians.pdf)” to determine whether a prospective subject has or has not attained the legal age for consent to treatments or procedures involved in the research under the applicable law of the jurisdiction in which the research will be conducted. (e.g., individuals under the age of 18 years). If this SOP will not be followed, describe how this (attainment of legal age for consent or not) will be determined:
2. How permission to participate in the study will be obtained from the parents or legal guardians:
3. The assent process of children as follows:
   1. Any waiting period available between informing the prospective subject and obtaining the assent:
   2. Any process to ensure ongoing assent:
   3. Research team members involved in the assent process:
   4. How long children will have to consider study participation:
   5. Steps that will be taken to minimize the possibility of coercion or undue influence:
   6. Steps that will be taken to ensure the subjects’ understanding:
   7. If assent will not be obtained from children, specify why:
   8. If children reach 18 years of age while in the study describe the following:
      1. The plan to obtain written informed consent from the subject at age 18 years:
      2. Who will be responsible for managing the plan:
      3. Where the consent discussion will take place:
      4. What will happen if the subject cannot be located to provide consent at age 18 years:
4. Can or will minors who are:
5. married, widowed, divorced; or
6. the parent of a child; or
7. a member of any of the armed forces; or
8. pregnant or believes herself to be pregnant; or
9. living separate and apart from his/her parent or legal guardian, and is managing his/her own financial affairs

be approached for study participation for either themselves or their child?

**Yes  No**

If **Yes**, respond to all of the following:

1. How will it be determined that this population has the capacity to consent for this study. Please note that the circumstance of parenthood, pregnancy, etc. may not mean that the person has the same capacity of an adult who can understand the risks, benefits, and alternatives for indicated care. Thus, sound and sensitive clinical judgment that is attentive to both the minor’s rights and the minor’s actual competence and needs must be considered, and is to include a determination as to whether involvement of family or other adults familiar to the minor is necessary and appropriate:
2. How informed consent will be executed with this population in a way that allows for independent and thoughtful decision-making:
3. Any additional steps or procedures that will be used when performing informed consent with this population:

Refer to Massachusetts state law ([MGL Chapter 112, Section 12F](http://www.malegislature.gov/Laws/GeneralLaws/PartI/TitleXVI/Chapter112/Section12F)) for more information about this population. Please note, the statute applies to clinical care and should be applied to research only as applicable.

1. Can or will wards of the state and/or children at risk of becoming wards of the state be enrolled (this includes foster children or any child that is in state custody)?

**Yes  No**

If **Yes**, respond to all of the following:

1. *Justification for recruiting and enrolling this population:*
2. *Any additional details about the recruitment methods to be used. If the same recruitment methods previously described in the protocol will be used, then state that:*
3. *Any additional details about the informed consent process to be used. If the same informed consent process for enrolling minors previously described in the protocol will be used, then state that:*
4. *How it will be ensured that the appropriate person(s) grants permission for each ward to participate in the research:*
5. *How the research team will know if there has been a change in guardianship status during the course of the research and how permission will be obtained from the new guardian:*
6. *Check to confirm that documentation of review by the Department of Children and Families (DCF) for this study has been submitted to the IRB.*
7. *If the study is greater than minimal risk, describe the following* or  N/A, study is not greater than minimal risk:
8. *Whether the research is related to their status as wards OR if the research is conducted in schools, camps, hospitals, institutions, or similar settings in which the majority of children involved as subjects are not wards:*
9. *How an advocate will be appointed for each child who is a ward, in addition to any other individual acting on behalf of the child as guardian or in loco parentis:*
10. *The background and experience of the advocate to act in the best interests of the child for the duration of the child’s participation in the research:*
11. **☐***Check to confirm that the advocate will not be associated in any way (except in the role as advocate or member of the IRB) with the research, the investigator(s), or the guardian organization.*

Refer to the IRB’s [Wards of the State policy](https://viceprovost.tufts.edu/tufts-health-sciences-irb-policy-wards-state) for additional information on enrolling wards of the state.

1. Can or will cognitively impaired adults (adults with impaired-decision making capacity) or adults who may lose the capacity to consent be enrolled?

**Yes  No**

1. Can or will prisoners be enrolled?

**Yes  No**

If **Yes**, respond to all of the following:

1. *Any possible advantages accruing to the Prisoner through his or her participation in the research, when compared to the general living conditions, medical care, quality of food, amenities and opportunity for earnings in the prison, are not of such a magnitude that his or her ability to weigh the risks of the research against the value of such advantages in the limited choice environment of the prison is impaired:*
2. *Whether the risks involved in the research are commensurate with risks that would be accepted by non-Prisoner volunteers:*
3. *Procedures for the selection of subjects within the prison which are fair to all Prisoners and immune from arbitrary intervention by prison authorities or Prisoners. Unless the Principal Investigator provides to the Board justification in writing for following some other procedures, control subjects must be selected randomly from the group of available Prisoners who meet the characteristics needed for that particular research project:*
4. *Check to confirm that parole boards will not take into account a Prisoner’s participation in the research in making decisions regarding parole, and each Prisoner is clearly informed in advance that participation in the research will have no effect on his or her parole.*
5. *Check to confirm that a letter of support from the Prison this research will be conducted in has been submitted to the IRB.*
6. *If follow-up examination or care of subjects after the end of their participation is required, describe the provision for such examination or care, taking into account the varying lengths of individual Prisoners’ sentences, and for informing subjects of this fact:*
7. Can or will students and/or employees be **targeted** for enrollment in this research?

**Yes  No**

If **Yes**, respond to all of the following:

1. Justification for specifically targeting recruitment efforts to enroll students and/or employees:
2. How potential coercion will be eliminated:
3. Recruitment methods to be applied specifically to students and/or employees. If the same recruitment methods previously described in the protocol will be used, then state that:
4. Additional safeguards included to protect the rights and welfare of students and employees:
5. Protections to ensure that a subject’s decision about participation and/or early withdrawal from the study will not affect his/her status as a student or employee:
6. Check to confirm that you have submitted a letter from the appropriate institutional official (e.g., Department Chair, Dean, Vice-President) who oversees the students and/or employees attesting to the fact that the employee’s or student’s participation in the research is acceptable and that coercion has been minimized.
7. Transgender Subjects: Are you recording sex or gender for your study?

**Yes  No**

Is there a scientific and/or safety rationale for collecting information on whether a subject is transgender?  Yes  No

If **no**, there is no scientific or safety-related rationale for needing to identify sex or gender for your study, and you will not collect information on transgender and gender nonconforming people’s identification.

# Adverse Event Monitoring

## H.1 Definitions

*Define adverse events (AEs), serious adverse events (SAEs), and unanticipated problems for your study:*

The study does not anticipate any adverse events as there is no experimental procedure or intervention being performed.

##

## H.2 Reporting Procedures

1. *Describe the protocol-specific reporting procedures, including who will be responsible for each step (e.g., PI, Data Coordinating Center, Medical Monitor), which forms should be completed, timeframes for reporting, how reports will be distributed, and what follow-up is required: NA*
2. *Include specific details of reporting procedures for:*
   1. *Deaths, life-threatening events, pregnancies: NA*
   2. *Other SAEs: NA*
   3. *Other AEs: NA*
   4. *Other UPs: NA*

Ensure that the reporting procedures meet the reporting requirements of the FDA, NIH, OHRP, sponsor, study leadership and any other regulatory body that applies to the study, as applicable.

##

## H.3 Reportable New Information

*Check to confirm that reportable new information will be reported to the IRB per the Tufts Health Sciences IRB’s* [*Reportable New Information policy.*](https://viceprovost.tufts.edu/reportable-new-information) *If your reporting plan to the IRB differs from the IRB’s policies, please describe it in detail or specify where this information is in the protocol:*

# Statistical Considerations

##

## I.1 Study Endpoints

1. Describe the primary and secondary study endpoints:

The primary outcome of interest is the overall diagnostic accuracy of the automated LVEF, stroke volume, and cardiac output computation as compared to either TTE (for LVEF assessments) or right heart catheterization (for stroke volume and cardiac output assessments).

1. Describe any primary or secondary safety endpoints:

- Time to LVEF acquisition with FoCUS

##

## I.2 Sample Size Justification Statistical Analyses

1. Describe the statistical analyses that will be performed for this study:

All patients who are enrolled will be included in the analysis and the data will be analyzed according to the intention-to-treat principle, with the exception of patients who are found to have moderate or greater regurgitant valvular disease following enrollment. Continuous variables will be summarized as either mean and standard deviation or median and interquartile range, as appropriate. Categorical variables will be summarized by frequency and percentage. The Chi-square or the Fisher’s exact test will be used to compare discrete variables, and the Student’s *t* test or Mann-Whitney U-test will be used to compare continuous variables, as appropriate.

First, the differences between the FoCUS and TTE LEVFs, and the differences between the FoCUS and right heart catheterization stroke volumes and cardiac outputs, will be evaluated for normality bot visually and statistically. This will be done by visual evaluation of quantile-quantile plots, and by applying the Shapiro-Wilk test.^11^ Second, we will evaluate for the presence of proportional bias by performing a regression analysis.^12^ Third, in the case of paired measurements (i.e. if a patient has more than one FoCUS examination performed), we will perform a test for autocorrelation. If the autocorrelation is determined to be non-negligible a correction for the use of paired measurements will be applied.^12^ Finally, the agreement between the FoCUS and TTE LVEF’s will be evaluated through the construction of a Bland-Altman plot along with the mean difference (bias), 95% limits of agreement (LOA), and mean error – along with their corresponding 95% confidence intervals.^13^

1. Provide a sample size justification:

Based on a 95% agreement between FoCUS and formal echocardiography, and a 5% error margin, we anticipate that we would need 73 patients with adequate windows to obtain an AI LVEF. As not all patients may have adequate windows to calculate a biplane method of disks summation (modified Simpson’s rule) and individuals may be found to have moderate or great regurgitant valvular disease following formal TTE, we will aim to recruit 130 patients for the LVEF component of this project.

Based on a 90% agreement between FoCUS and right heart catheterization, and a 10% error margin, we anticipate that we would need 35 patients with adequate windows to obtain an AI stroke volume or cardiac output. As not all patients may have adequate windows to calculate a biplane method of disks summation (modified Simpson’s rule), we will aim to recruit 70 patients for the stroke volume and cardiac output component of this project.

Therefore, in total, we plan to recruit 200 patients for this study.

##

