# Study Design

## F.1 Study Timelines

- 1. Describe the duration of an individual subject’s participation in the study:

Participants will be required to allow a Focused cardiac ultrasound be performed at the time of enrollment. Following this study there is no further requirement from the subject. The research team will follow up on the results of the subjects formal echocardiogram and/or right heart catheterization by reviewing the patient’s medical records if it is not available at the time of enrollment. After this information has been collected the subject’s participation will cease.

- 1. Describe the duration anticipated to enroll all study subjects at the Tufts study site:

12 months

- 1. Describe the estimated date for investigators to complete this study (complete primary analyses):

December 2021.

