## F.2 Procedures

1. If **Yes**, respond to all of the following:
2. *Describe the scientific, methodological, and medical reasons to use a placebo:*
3. *Describe the care that will be given to subjects who receive placebo. If this is local standard of care, specify that:*
4. *Describe all potential risks to the placebo group and how the risks will be minimized.*
5. *Summarize the research design and sequentially identify all procedures to be performed to accomplish the specific aims of the project. Clearly identify and distinguish procedures that are considered experimental, procedures that are performed exclusively for research purposes (including “extra” routine tests), and procedures that would occur regardless of the research (i.e., standard of care). Point out any procedures, situations, or materials that may be hazardous, and the precautions to be exercised to maintain subject safety:*

This is a prospective cohort study. Consecutive patients cared for at Tufts Medical Center, who have had a recent (within 30 days), or are scheduled to have a subsequent TTE performed at the discretion of the treating team will be screened for participation. Also, patients who are undergoing a right heart catheterization for a clinical indication will also be eligible for recruitment.

We will prospectively collect baseline clinical and demographic characteristics at the time of enrollment. We will be accessing the electronic medical record (Sorian) and entering the information collected into RedCap. There will be no collection of data beyond the date of enrollment, with the exception of those patients whose TTE or right heart catheterization has yet to be performed, in which case the subsequent TTE/right heart catheterization report will be the only information collected prospectively beyond the day of enrollment. The specific procedures to be followed will be:

- Patients who have had a recent TTE (within 30 days), or are scheduled to have a TTE and/or right heart catheterization performed for clinical reasons are eligible to participate in this study.
- If agreeable to participate in the study then participants will receive the usual standard of care (right heart cath and/or TTE) as dictated by the treating medical team.
- Upon signing the consent form, the research team will begin to collect baseline clinical and demographic information about participants from them and/or their medical chart.

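### Minor: the correction for repeat FoCUS exams on one patient depends on an autocorrelation pre-test with no stated threshold; fix one exam per patient in advance, or always correct.

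*Protocol*

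**What the plan says.** The rule is in protocol section I.2, as the third step of the agreement analysis. The pre-test comes first: "if a patient has more than one FoCUS examination performed), we will perform a test for autocorrelation". The consequence follows: "If the autocorrelation is determined to be non-negligible a correction for the use of paired measurements will be applied". The section names no specific test, no significance level and no size of correlation that would count as non-negligible.

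The planned number of exams is one. Section F.1 says "Participants will be required to allow a Focused cardiac ultrasound be performed at the time of enrollment" and asks nothing more of the participant after that, and the procedures in F.2 list a single KOSMOS evaluation. F.2 also says the bedside scan is performed to guide clinical care, except in participants who come as outpatients. Repeats are therefore possible, but they are not scheduled.

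**The concern.** Two exams on one patient share that patient's anatomy, image quality and physiology, and may share one reference reading as well. Their FoCUS-minus-reference differences should be expected to correlate because of how the data arise. A significance test adds little to that knowledge, and a non-significant result from a handful of pairs is not evidence of independence.

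Under the protocol's rule, however, such a result leaves the repeat exams uncorrected. The number of observations is then overstated and the confidence interval for the mean difference is too narrow. Because no threshold is fixed, the choice between the two analyses is also made after the data have been seen.

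**Working it through.** **The protocol's own figures.** The sample sizes in I.2 reproduce as the precision of a single proportion, n = z²p(1−p)/d², assuming two-sided 95% confidence (z = 1.96):

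- LVEF: p = 0.95, d = 0.05 gives 72.99, so 73.
- Stroke volume and cardiac output: p = 0.90, d = 0.10 gives 34.57, so 35.

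Both count one observation per patient. They are not in dispute and serve below as the numbers of evaluable patients.

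**Assumptions not in the protocol.** These are: 10% to 100% of patients have one second exam; the within-patient correlation ρ of the differences is 0.3 to 0.7; the differences are normal; and the pre-test is a two-sided 5% test of the correlation across the k repeat pairs, t = r√((k−2)/(1−r²)). The final Bland-Altman step in I.2 names only LVEF, so the 35-patient case further assumes that the same interval for bias is computed against catheterization.

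**What ignoring repeats does, by formula.** With n patients, k of them repeated, and N = n + k exams, the variance of the mean difference is (σ²/N)(1 + 2kρ/N). Treating exams as independent omits the bracket. With 20% repeated and ρ = 0.5:

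- n = 73, k = 15, N = 88: bracket 1 + 15/88 = 1.170, square root 1.082. Coverage is about 2Φ(1.96/1.082) − 1 = 93.0%.
- n = 35, k = 7, N = 42: bracket 1 + 7/42 = 1.167, square root 1.080. Coverage is about 93.0%.

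**What the two-stage rule does, by simulation.** There were 20,000 runs per cell, so the Monte Carlo standard error is about √(0.95 × 0.05/20,000) = 0.15 percentage points. The uncorrected interval uses SD/√N. The corrected one uses a cluster-robust standard error. The rule uses the corrected interval only when the pre-test is significant.

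| n | Share repeated | ρ | Pre-test power | Coverage, ignore | Coverage, rule | Coverage, always correct |
|---|---|---|---|---|---|---|
| 73 | 20% | 0.5 | 49.7% | 93.2% | 94.4% | 95.0% |
| 35 | 20% | 0.5 | 21.3% | 93.1% | 93.7% | 94.7% |
| 35 | 30% | 0.5 | 32.4% | 92.0% | 93.1% | 94.4% |
| 73 | 100% | 0.5 | 99.7% | 88.8% | 95.0% | 95.0% |

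The simulated ignore column in the first two rows agrees with the formula. The third row is the worst cell for the rule. Over the whole grid, the rule gives 93.8% to 95.0% at 73 patients and 93.1% to 94.9% at 35. Always correcting gives 94.4% to 95.2%.

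**What one exam per patient would cost.** In units of σ, the standard error from the first exam only is √(1/73) = 0.1170. From all 88 exams, correctly analysed, it is √(1.170/88) = 0.1153, a loss of about 1.5%. At 35 patients it is √(1/35) = 0.1690 against √(1.167/42) = 0.1667, about 1.4%.

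**The case against.** The strongest reply is that this hardly matters. One exam per participant is planned, the number of repeats is unknown, and with none the rule is never used. Where repeats are many the pre-test nearly always fires, and where they are few they carry little weight. All of this stands, and it is why the point is minor.

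A second reply is that non-negligible may mean a judgement on the size of the correlation and not a 5% test. That is possible, and the power figures above would then not apply. The decision would still be taken on the observed data against no fixed standard. A statistical analysis plan might supply a threshold, but a threshold would not cure the conditional structure, which the protocol itself sets.

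Two stronger readings are tempting, and the protocol supports neither.

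- A reader might infer that repeats will simply be ignored, with coverage falling below 90%. That needs many repeats and no correction. With all 73 patients repeated and ρ = 0.5, the pre-test fires 99.7% of the time and coverage is 95.0%.
- A reader might infer that paired readings will be compared with independent-samples tests, since I.2 says "test or Mann-Whitney U-test will be used to compare continuous variables, as appropriate" and F.2 says "This is a prospective cohort study". That sentence is general, names no groups and is not tied to KOSMOS against a reference. Student's t is not said to be unpaired, and a single cohort can contain subgroups for which two-sample tests are valid. The method comparison works on within-patient differences: "the differences between the FoCUS and right heart catheterization stroke volumes and cardiac outputs, will be evaluated for normality", and LVEF is treated likewise and goes on to a Bland-Altman analysis with a confidence interval for the mean difference.

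**Conclusion.** The point holds as a minor one. Making the correction conditional on an undefined pre-test is worse than either fixing one exam per patient or always correcting. The worst coverage found for the bias interval is 93.1%, about 2 points below nominal; the largest gap to always correcting is 1.6 points (93.3% against 94.9%, at 35 patients, all repeated, ρ = 0.3). These figures rest on assumed repeat shares, correlations and a 5% pre-test, and they concern the interval for bias only; the intervals for the limits of agreement were not simulated. Neither the sample sizes nor the paired basis of the method comparison is called into question.

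**What to change.** Delete the autocorrelation pre-test from I.2 and replace it with one of two rules, chosen before the data are examined:

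- the primary analysis uses one pre-specified exam per patient, the first complete one, with any later exams kept for a secondary analysis; or
- whenever any patient contributes more than one exam, all exams are used and the repeated-measures correction is always applied.

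The first is simpler and matches the one-observation-per-patient basis of the sample size. In the 20% example it costs about 1.5% in standard error. The second gives an interval about 8% wider than the uncorrected one in that example (the factor of 1.082 above), which is the width the data warrant. Either way the change is to analysis wording only, with no effect on enrolment or procedures.
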